### Inclusion and exclusion criteria

The *inclusion criteri*a for pain samples are non-specific chronic musculoskeletal pain lasting for ≥ 45 days during the past three months, at least 18 years of age, and fluent German language skills. All control participants (participants with PTSD, depression, and healthy controls) should be pain-free. Because the point prevalence of back pain in the German population was more than one third and the 1-year prevalence was higher than 75% [57], the recruitment of patients that were absolutely pain free within the last three months, will not be feasible and will not reflect reality. Therefore, we aim to recruit only absolutely pain-free participants. If this is not possible, we will define pain-free as follows: 1) less than one day (< 24 hours) spent in pain per week within the last three months. 2) Pain intensity < 3 on an 11-point numeric rating scale on the days when the patient is in pain. 3) Pain does not interfere with normal activities or work. These criteria are adapted from standardised definitions of back pain [59] and its recurrence [60]. Participants must also be pain free on the day of participation in the study. Patients who have a previous history of chronic pain will be excluded. Participants with PTSD and depression must fulfill DSM-IV diagnoses of the respective mental disorder. Patients with PTSD must be free of affective disorders, and patients with depression must be free of anxiety disorders. Healthy controls are not allowed to meet any DSM-IV diagnosis. The *exclusion criteria* are specific pathologies of CBP (e.g., spinal canal stenosis, disc hernia, spondylolisthesis, infection, malignancy, rheumatic and systematic inflammatory disorders, and fracture), sciatica pain ≥ than back pain, diseases affecting sensory processing (diabetes, alcohol or substance abuse, neuropathy, inflammatory diseases), pain or surgery at the dorsum of the hand or back surgery in the past three years (because the hand und back are to be subjected to investigation), and cognitive impairment.

### Procedure

#### Chronicity of pain

The number of painful days in the last three months will be determined by a questionnaire and discussed with a physician to rule out misunderstandings. To be classified as suffering from chronic pain, the subject must report experiencing back pain on ≥ 45 days in the last three months.

#### Clinical examination

To verify the inclusion and exclusion criteria, all participants will be questioned about their past medical history and about co-morbidities (neuropathy, diabetes, relevant alcohol consumption, infections, inflammatory diseases, disc hernia, previous severe injuries). Patients will also receive a physical examination (general, rheumatological, orthopaedic, and neurological), including blood tests (and if indicated further technical investigations such as x-ray or MRI) with special attention paid to findings that indicate a specific origin of back pain. Therefore, the “red flags” (hints of the presence of serious pathology according to the Agency for Health Care Policy and Research Low Back Guidelines) and yellow flags will be considered [61], and former medical reports and discharge letters will be taken into account whenever available. In the case of signs of serious pathological findings, participants will be excluded, and a further investigation will be advised. Painful tender points will be identified by tenderness examination using ACR criteria [62].

#### Measures of clinical manifestation

The clinical manifestations of pain will be considered using the pain dimensions (pain intensity, pain location/ extent, pain quality, and pain affect), disability/ impairment (subjective as well as objective measures), and psychological measures (mental comorbidity, early life stress, health-related quality of life, and resilience). Patients will be clustered in homogeneous groups according to their clinical manifestation. In subsequent analyses, we will test whether the clinical manifestation corresponds with specific mechanisms (see below).

#### Pain dimensions

There are at least four dimensions of pain experience that can be distinguished. These are intensity, location, quality, and affect. *Pain intensity*: Pain intensity is defined as how much a person hurts. It will be measured using a numerical rating scale, ranging from 0 ‘no pain’ to 10 ‘worst pain imaginable’. *Pain location*: Pain location can be defined as the perceived location(s) of pain sensations that patients have on or in their body. Spatial distribution patterns (local vs. referred pain) will be assessed using a digitised pain drawings [63]. Moreover, categorisation as CLP, CWP, and FMS will be based on the ACR criteria [62] and a more precise definition elaborated by Harkness et al. [6]. Therefore, each participant will be asked to complete a body pain diagram, marking all areas where pain is experienced. Afterwards, the pain diagram will be discussed jointly by the participant and the physician to rule out any misunderstandings. *Pain quality and pain affect*: Pain quality refers to the specific physical sensations associated with pain. Pain affect is the degree of emotional arousal caused by the sensory experience of pain. The affective and sensory dimensions of pain will be measured using the Pain Experience Scale (SES). The SES is the standard instrument of the German chapter of the International Association for the Study of Pain. The SES consists of 10 items on a sensory subscale (e.g., ‘throbbing’, ‘wrenching’ or ‘stinging’) and 14 items on an affective subscale (e.g., ‘exhausting’, ‘fearful’, or ‘unbearable’). The response format is a four-stage format (0 ‘not appropriate’; 1 ‘somewhat appropriate’; 2 ‘generally appropriate’; 3 ‘fully appropriate’). The sensory score of the SES is the mean of all sensory items; the affective score of the SES is the mean of all affective items. The retest-reliability of the SES lies between .89 and .96, and Cronbach’s Alpha lies between .72 and .92 [64].

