### Design

The study uses a descriptive and exploratory design. We will include 200 patients with chronic musculoskeletal pain from different settings (a population-based setting and a tertiary care setting) and 90 controls (pain-free patients with PTSD, depression, and healthy controls without mental disorders). All participants will undergo a physical examination. The relevant sociodemographics and measures of clinical manifestations of chronic pain are reported in Table 1: measurements of potential pathophysiological mechanisms are reported in Table 2.

**Table 1 T1:** Variables and methods used to assess clinical manifestations of chronic non-specific musculoskeletal pain

**Questionnaires**	**Variables**
Chronic Pain Grade Questionnaire (CPG)* [65,66]	Severity of chronic pain problems (disability, pain intensity)
Pain Experience Scale (SES) [64]	Sensory and affective descriptors of pain
12-Item Short-Form Health Survey (SF-12)* [74,75]	Health-related quality of life
Resilience Scale (RS11)* [97,98]	Resilience (personal competence, acceptance of self and life)
Hospital Anxiety and Depression Scale (HADS-D)* [99,100]	Anxiety and depression
Childhood Trauma Questionnaire (CTQ)* [72,73,101]	Childhood and adolescence maltreatment (physical and emotional abuse, sexual abuse, physical and emotional neglect)
Pain drawing (pain location) [62][63][6]	Perceived location(s) of pain will be assessed using digitised pain drawings. Classification into categories of chronic local and chronic widespread pain.
Sociodemographics (self-report questions)	Age, sex, marital status, education, employment status

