**Physical examination**	
ACR Criteria for Fibromyalgia (ACR Classification) [62][102]	Tenderpoint count and documentation of specific symptoms
Physical Impairment Scale (PIS) [67]	Physical impairment (total flexion, total extension, average lateral flexion, straight leg raising, spinal tenderness, bilateral active straight leg raising, and sit-up)
Back Performance Scale (BPS) [68]	Disability. Tests of daily activities (Sock Test, Pick-up Test, Roll-up Test, Fingertip-to-Floor Test, and Lift Test)

* German Version.

**Table 2 T2:** Methods used to assess the potential mechanisms involved in chronic non-specific musculoskeletal pain

**Measures**	** *Variables* **
Quantitative Sensory Testing (QST) [76,103]	Comprehensive profiles of somatosensory functions (thermal and mechanical detection and pain thresholds, vibration thresholds, and pain sensitivity to sharp and blunt mechanical stimuli). Discrimination between local vs. generalised and peripheral vs. central nervous mechanisms.
Conditioned Pain Modulation (CPM, the diffuse noxious inhibitory control-like effect) [77,78]	A descending pain inhibitory mechanism that inhibits nociceptive activity arising from the afferent primary fibres at multiple levels of the dorsal horn, resulting in diffuse pain inhibition. These descending pain pathways originate from the brainstem and have significant inhibitory actions on nociceptive activity, thereby affecting pain perception.
*Blood Tests*	
Nerve Growth Factor (NGF)	Plasma NGF levels (proximity ligand ELISA techniques)
Endocannabinoids + related lipids (ECs)	EC (anandamide (AEA), 2-arachidonoyl glycerol (2-AG), 1-arachidonoly glycerol (1-AG), palmitoyl ethanol amine (PEA), oleoyl ethanol amine (OEA), arachidonic acid) in human plasma (large- scale lipidomic profiling using the LC-MS/MS QTrap ABI5500)
Genetics	2* 9 ml EDTA tubes, stored for the second funding period

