#### Psychophysiological mechanisms

##### Quantitative Sensory Testing (QST)

Somatosensory function will be assessed using the comprehensive *QST* protocol developed as part of the German Research Network on Neuropathic Pain (DFNS). Seven tests measuring 13 parameters (warm detection threshold, cold detection threshold, thermal sensory limen, paradoxical heat sensation, cold pain threshold, heat pain threshold, mechanical detection threshold, mechanical pain threshold, mechanical pain sensitivity, dynamic mechanical allodynia, wind-up ratio, vibration detection threshold, and pressure pain threshold) [76] will be conducted. QST testing covers all relevant aspects of the somatosensory system including large and small fibre function as well as signs of central sensitisation (dynamic tactile allodynia, punctate mechanical hyperalgesia). This way, detailed profiles of somatosensory function will be obtained for the tested body areas. The test sites will be distributed throughout the paraspinal muscles (5 cm ± 0.5 cm next to the midline on the autochthon back muscles [L1 to S1]) and on the dorsum of the ipsilateral hand.

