### Statistical analyses

Descriptive statistics will be presented with means and standard deviations for continuous variables and absolute numbers and percentages for categorical variables. Questionnaires will be dealt with according to questionnaire manuals. The prevalence of chronic local pain, chronic widespread pain, fibromyalgia, and mental comorbidities will be determined for the population-based sample and tertiary care setting. Explorative cluster analysis will be conducted to establish subgroups based on the clinical manifestations observed. Therefore, the dimensions of pain (see above) and mental comorbidity will be used as cluster variables. Then, we will explore whether different neurobiological profiles (QST profiles, CPM, NGF levels, EC profiles) correspond with these subgroups. Pain drawings will be scanned, superimposed, and transformed into two-dimensional color-coded images. Body areas with high occurrence of pain will be illustrated in dark red; body areas without pain will appear in white. To classify patients who suffer chronic local pain (CLP) or chronic widespread pain (CWP), pain drawings will be analysed according to the ACR criteria [62] and a more precise definition [6]. Quantitative sensory testing (QST) data pre-processing and statistical analysis will be performed according to the protocol established by Rolke et al. [76]. To quantify conditioned pain modulation (CPM), the PPT before PHP will be subtracted from the PPT after PHP. Negative values indicate an analgesic effect due to CPM. Differences between patient groups will be analysed using analyses of co-variance (ANCOVA), followed by Fisher’s least significant difference test. Potential confounders will be included as covariates, if indicated. QST modalities or CPM will be entered as dependent variables, the patient groups as an independent variable. For more detailed information analysing QST data, we will refer to the protocol proposed by Rolke et al. [76]. The same procedure will be applied with regard to nerve growth factor (NGF) and endocannabinoids (ECs).

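### Fibromyalgia rests on a tenderness examination and is listed under pain location, a cluster input, so part of any pressure pain threshold difference may follow from the group definition

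*Protocol article*

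**What the plan says.** All references are to the protocol article.

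- **How FMS is assessed.** Table 1 (physical examination) lists the ACR criteria for fibromyalgia with "Tenderpoint count and documentation of specific symptoms". The Clinical examination section says that the tender points are found by a tenderness examination.
- **Where FMS is placed.** The Pain dimensions section names four dimensions. Under pain location it says that "categorisation as CLP, CWP, and FMS will be based on the ACR criteria [62] and a more precise definition".
- **What is clustered.** Statistical analyses says that "the dimensions of pain (see above) and mental comorbidity will be used as cluster variables". Measures of clinical manifestation gives a wider basis: "Patients will be clustered in homogeneous groups according to their clinical manifestation". It counts disability and impairment among those manifestations, and the Physical Impairment Scale (PIS) has a spinal-tenderness item.
- **What is compared.** Statistical analyses then explores whether QST profiles, conditioned pain modulation (CPM), nerve growth factor (NGF) and endocannabinoids (ECs) correspond with the subgroups. The 13 QST parameters end with "vibration detection threshold, and pressure pain threshold".
- **What points the other way.** For the pain drawing, Table 1 gives "Classification into categories of chronic local and chronic widespread pain". Statistical analyses agrees: "To classify patients who suffer chronic local pain (CLP) or chronic widespread pain (CWP), pain drawings will be analysed according to the ACR criteria". Neither names FMS as a level of location. Statistical analyses mentions fibromyalgia only as a prevalence to be reported.

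**The concern.** Objective 2 asks whether clinically defined subgroups have distinct sensory profiles because their mechanisms differ. That requires the clinical side and the mechanism side to be measured separately. If a tenderness criterion helps to form the groups and PPT is then compared between them, one property sits on both sides. Patients selected for tenderness would tend to show lower PPT even if FMS and CWP were one population with one mechanism. Such a difference would be real, but it would describe the case definition and would not show a distinct mechanism. The article neither mentions this overlap nor plans an analysis without the tender points.

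**Working it through.** The plan gives no figure to reproduce. It states no significance level, no share of CWP patients with FMS and no tender-point/PPT correlation. The check asks how large the built-in part could be.

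**Inputs from the article.** 200 pain patients (Design); 61.8% CLP and 38.2% CWP (Sample size estimation). Hence 200 × 0.618 = 123.6 CLP and 200 × 0.382 = 76.4 CWP.

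**Assumptions.** A tenderness examination elicits pain on pressure. FMS is CWP plus tenderness above a cut-off. A share q = 25% or 50% of CWP qualifies. r is the size of the correlation between tenderness and PPT (higher tenderness, lower PPT). Nothing else links PPT to the groups. The test is two-sided at 0.05. The CWP share comes from the population-based study and is applied to all 200, half of whom come from tertiary care.

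**1. Expected PPT shift, FMS against CLP, in SD units.**

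Shift = r × φ(z)/q, with z the upper-q point of the standard normal.

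- q = 25%: φ(0.674)/0.25 = 0.318/0.25 = 1.27
- q = 50%: φ(0)/0.5 = 0.399/0.5 = 0.80

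| r | q = 25% (simulated) | q = 50% (simulated) |
|---|---|---|
| 0.3 | 0.38 (0.39) | 0.24 (0.25) |
| 0.5 | 0.64 (0.63) | 0.40 (0.40) |
| 0.7 | 0.89 (0.89) | 0.56 (0.56) |

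**2. Direct comparison of FMS, CWP and CLP.** Chance of p < 0.05 in a three-group ANOVA on PPT, 1,500 simulated studies per row and share:

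| r | q = 25% | q = 50% |
|---|---|---|
| 0 | 5.2% | 4.5% |
| 0.3 | 38.8% | 46.5% |
| 0.5 | 84.1% | 91.0% |
| 0.7 | 99.1% | 99.9% |

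CWP against CLP from the drawing alone, over all settings run: 4.2-5.6%.

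**3. FMS as one level of one of five cluster inputs.** K-means with k = 3 or 4 on three correlated pain scores, a location code and a comorbidity indicator, then ANOVA on PPT; q = 50%; 500 simulated studies per cell.

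| r | FMS in, k = 3 / 4 | FMS out, k = 3 / 4 |
|---|---|---|
| 0 | 3.4% / 3.6% | 5.6% / 4.2% |
| 0.3 | 7.0% / 9.6% | 5.4% / 3.4% |
| 0.5 | 9.0% / 16.4% | 4.4% / 4.4% |
| 0.7 | 16.0% / 26.6% | 5.6% / 5.2% |

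The simulation error near 5% is √(0.05 × 0.95/500) ≈ 1 percentage point. So 7.0% against 5.4% at r = 0.3 with three clusters is within noise, while the gaps at r = 0.5 and 0.7 are not. The 25% share was not run in the clustering.

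**4. Reach.** PPT is 1 of 13 QST parameters. CPM is a within-person change in PPT, so a lower starting level does not by itself shift it. NGF and ECs share no measurement with the tender-point count.

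**The case against.** The best defence is that FMS was never meant as a cluster input. Pain location is defined by where patients feel pain, the sentence naming FMS is followed by the body diagram, and both Table 1 and Statistical analyses limit the drawing to CLP and CWP. An article may also leave the exact input list to a fuller document. This stands in part: FMS in the clustering is one reading, not an established fact. But the sentence under pain location does name FMS, Statistical analyses points back to those dimensions, and Measures of clinical manifestation names a wider basis. The stated passages disagree, and that is more than an omitted detail.

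Three further points stand as limits:

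- Clustering on several variables dilutes the effect, as step 3 shows.
- PPT is measured at the paraspinal muscles and the hand, so its overlap with the tender-point count is a correlation of unknown size and not the same measurement.
- The PIS item is one of seven summed 0/1 items and matters only on the wider clustering basis.

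The design is also declared exploratory. That lowers the stakes, but it does not make an overlapping measure informative about mechanism.

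A reader might infer that the plan would read a low PPT in FMS as central disinhibition. The Background does not support this: it draws that inference from raised sensitivity across several pain modalities in all measured body areas.

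**Conclusion.** The point holds conditionally. If FMS, the tender-point count or the PIS tenderness item enters the clustering, or if FMS is compared directly with CWP or CLP, part of any PPT difference follows from the group definition. The direct comparison is possible because the ANCOVA does not define its patient groups.

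Under assumed correlations of 0.3 to 0.7, the chance of p < 0.05 from the definition alone is about 7-27% in the cluster analysis and about 39-100% in the direct comparison, against about 3-6% with FMS left out. These ranges rest on assumed correlations and FMS shares, so they show direction and rough size only.

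Two stronger conclusions are tempting. The first is that a whole distinct sensory profile is built in by selection. The documents do not support it, since one of 13 parameters is directly affected and NGF and ECs are untouched. The second is to take the direct-comparison percentages as the error rate of the planned cluster analysis. They belong to a different analysis, and the clustered figures are much smaller.

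**What to change.** 1. Reconcile Table 1, Measures of clinical manifestation, Pain dimensions and Statistical analyses into one list of cluster inputs.
2. In that list, build pain location from the pain drawing only (extent of pain, CLP or CWP). Leave out the FMS label, the tender-point count and the PIS spinal-tenderness item. At minimum, repeat the PPT comparison with these left out.
3. Still report FMS prevalence and any FMS contrasts. State that PPT in such a contrast overlaps the case definition and is not by itself evidence of a distinct mechanism.
4. Keep the other QST parameters as mechanism evidence, including mechanical pain threshold, mechanical pain sensitivity and allodynia, together with CPM, NGF and ECs.

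The cost is a change of wording and one input list, with no new data; the drawing-based rule is already in the article. The downside is small: PPT carries less weight in FMS contrasts, and FMS no longer shapes the clusters directly.

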#### Disability/ impairment

##### Chronic pain grade (CPG)

The CPG assesses the severity of chronic pain problems. It measures pain intensity and disability in regard to work and daily activities via patients’ self-reports. The CPG comprises 6 items that can be answered on an 11-point numerical rating scale ranging from ‘0’ to ‘10’. The number of days during which the patient experienced a disability during the past three months is assessed. Pain severity can be graded in four hierarchical classes (Grade I, low disability – low intensity; Grade II, low disability – high intensity; Grade III, high disability – moderately limiting; Grade IV, high disability – severely limiting). The CPG has proven reliability (α = .82) and validity [65,66]. To objectify impairment and disability, we will use the Physical Impairment Scale and the Back Performance Scale.

##### Physical impairment scale (PIS)

The PIS was developed as a simple and standardised clinical observation to evaluate physical impairment in patients with chronic low back pain. The test battery combines objective physical findings indicating current functional limitations due to pain. It consists of seven tests measuring lower back movement (total flexion, total extension and average lateral flexion as measured with the inclinometer), straight leg raises, spinal tenderness and strength (bilateral active straight leg raises, sit-ups). The measurements are translated into values of 0 or 1 according to cut-off values and summed. As subjective disability in non-specific low back pain is not explained by anatomic or structural impairment, the PIS measures functional limitation as influenced by the patient’s pain behaviour. The PIS is able to discriminate between pain patients and healthy controls and is related to self-reported disability in the activities of daily living [67].

##### Back performance scale (BPS)

The BPS is an objective clinical assessment tool that can be used to observe self-reported activity limitations in daily functioning caused by lower back pain. The BPS consists of five tests of daily activities (Sock Test, Pick-up Test, Roll-up Test, Fingertip-to-Floor Test, and Lift Test) frequently reported to be limited in back pain patients. Each performance is evaluated by the observer according to operational score definitions and then summed. The five tests are combined to obtain a performance measure of mobility-related activities requiring sagittal-plane mobility. The BPS is able to discriminate between pain patients with different return-to-work statuses and is sensitive to change. Cronbach’s α was .73 [68].

